### Data management

The therapists who will facilitate the groups and research assistants of the research project will be responsible for administering the paper questionnaires and entering the data electronically on a SPSS database. This database will be shared exclusively among the research teams at the University of Coimbra and the University of Lisbon, with access limited to the therapists, research assistants, and project coordinators. To ensure security, all electronic files will be password-protected, and physical copies of the questionnaires will be will be safely stored in locked file storage at each university. The data and research documents will be preserved for a period of 10 years following the conclusion of the study.

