##### Blinding

This clinical trial will be an open-label trial because both the researchers and the participants will know which treatment they receive. However, the participants will not know which intervention is the experimental condition and which is the control condition to avoid expectations about the efficacy of the new intervention and the comparison intervention.

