### Outcome measures

As depicted in Fig. 1, the parents and children will complete self-report questionnaires at baseline, mid-treatment (at 7 weeks for Emotion Detectives In–Out and 8 weeks for Coping Cat), posttreatment (at 15 weeks for Emotion Detectives In–Out and 16 weeks for Coping Cat), and follow-up (at 3 months). The (ADIS-IV-C) [44] will be administered at the screening phase, posttreatment, and follow-up.

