#### Primary outcome measures

##### Anxiety symptoms

Changes in anxiety will be assessed through the ADIS-IV-C [44] as well as the Revised Children’s Anxiety and Depression Scale (RCADS) – Child and Parent Versions [52]. The RCADS assesses children’s anxiety symptoms from the perspectives of the children and parents, respectively, and includes 47 items distributed across six subscales: Separation Anxiety Disorder, Social Phobia, Generalized Anxiety Disorder, Panic Disorder, Obsessive Compulsive Disorder, and Low Mood (major depressive disorder). The scales yield an anxiety total score (the sum of the 5 anxiety subscales) and a total score (the sum of all 6 subscales). Items are rated on a 4-point Likert scale ranging from 0 (*never*) to 4 (*always*), with higher scores indicating increased symptom severity.

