##### Symptom severity and improvement

The Clinician Global Impression – Severity scale [53] is a one-item measure that will be used to assess the clinician's perception of the severity of the children’s anxiety symptoms, with scores ranging from 1 (*not at all ill*) to 7 (*extremely ill*). Higher scores indicate increased symptom severity. The Clinician Global Impression – Improvement scale is also a one-item measure that will assess the clinician's perception of the children’s improvement as a result of the intervention, with scores ranging from 1 (*very much improved*) to 7 (*very much worse*). Higher scores indicate increased symptom worsening.

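### Group therapists share in administering and entering the self-report primary outcomes and can access the database; research assistants already named for the task could do this alone after allocation

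*Protocol article*

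**What the plan says.** Data management assigns questionnaire handling to two kinds of staff jointly: "The therapists who will facilitate the groups and research assistants of the research project will be responsible for administering the paper questionnaires". It makes the same staff responsible for "entering the data electronically on a SPSS database" and describes the database as shared between the two university teams, "with access limited to the therapists, research assistants, and project coordinators". It does not divide the work by group, arm or time point.

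The questionnaires are completed by children and parents at baseline, mid-treatment, posttreatment and 3-month follow-up (Outcome measures). Two of them, the RCADS and the CALIS in child and parent versions, stand under Primary outcome measures.

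The Blinding section calls the trial open label because "both the researchers and the participants will know which treatment they receive". One safeguard is kept: "the participants will not know which intervention is the experimental condition and which is the control condition". Nothing comparable is stated for those who collect data.

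Two clinician-rated instruments also stand under the primary heading. The ADIS-IV-C "will be administered at the screening phase, posttreatment, and follow-up", so two of its three administrations come after allocation. The CGI has a severity item and an improvement item; the latter "will assess the clinician's perception of the children’s improvement as a result of the intervention". The interviewer is described only for the eligibility interview (a clinical psychologist). The article does not say who gives the later ADIS-IV-C interviews or which clinician rates the CGI.

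**The concern.** Therapists know the arm and have a stake in how their groups fare. As written, a therapist may hand the RCADS and CALIS to the children and parents they have been treating, enter the answers, and see the accumulating outcome data. Answers given to the treating therapist may be kinder than answers given to someone else, and entry by an interested person is a second route for error. Data monitoring adds that there will be no auditing, so the article describes no independent check on what is entered.

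The Blinding section shows that the planners had expectation effects in mind, since families are not told which program is the new one. Staff who collect data get no matching protection.

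The design makes this more than a formality. In an equivalence trial, whatever makes the arms look more alike makes the sought conclusion easier to reach, so bias toward similarity is not conservative. Bias favouring one arm does the reverse when the arms are truly equal: it pushes the observed difference toward the margin and costs power.

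**Working it through.** **Inputs.** From Sample size: equivalence margin d = 0.50, TOST with alpha 0.05 per one-sided test, 80% power, 1:1 allocation, 69 per arm (138 in total), 15% attrition, about 165 recruited. From Statistical methods: between-group TOST at postintervention and at 3 months. The documents give no figure for rating or reporting bias, so every bias value below is an assumption.

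**Reproducing the plan's figures.** With true difference 0, n per arm = 2 × (z0.95 + z0.90)² / 0.50² = 2 × (1.645 + 1.282)² / 0.25 = 68.5, rounded up to 69, so 138 in total. For attrition, 138 / 0.85 = 162.4, or 163, against the stated 165 or so. Both figures stand and are not in dispute.

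**Probability of declaring equivalence.** In SD units the standard error is √(2/69) = 0.170. If the expected observed difference is d,

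P = Φ((0.50 − d)/0.170 − 1.645) − Φ((−0.50 − d)/0.170 + 1.645).

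At d = 0 this is Φ(1.292) − Φ(−1.292) = 80.4%, the planned power. At d = 0.50 it is 5.0%, the nominal error rate.

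**Scenario A: bias toward similarity, true difference at the margin (0.50).**

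| Assumed shrinkage | Expected observed difference | Equivalence falsely declared |
|---|---|---|
| none | 0.50 | 5.0% |
| 10% | 0.45 | 8.8% |
| 20% | 0.40 | 14.5% |
| 30% | 0.35 | 22.2% |
| 40% | 0.30 | 31.8% |

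For the 20% row: (0.50 − 0.40)/0.170 − 1.645 = −1.06, and Φ(−1.06) is about 14.5%; the second term is negligible. A t-based simulation gives 14.4% at 0.40 and 31.6% at 0.30.

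**Scenario B: bias favouring one arm, arms truly equal.**

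| Assumed differential bias (SD) | Power to declare equivalence |
|---|---|
| 0 | 80.4% |
| 0.1 | 72.9% |
| 0.2 | 54.0% |
| 0.3 | 31.8% |

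These are figures for one outcome at one time point. They show how sensitive the TOST is to bias of a given size. They do not estimate how much bias therapist involvement would cause.

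**The case against.** The strongest reply is that the text says less than one is tempted to read into it. Data management names therapists and research assistants together, so therapists are not the only collectors, and nowhere is it stated that a child's own therapist collects that child's forms. A condensed article may leave the assignment of assessors to the full protocol. This stands as a limit: the point is that the printed assignment permits the conflict, not that it will occur for every child.

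A reader might go further and infer that treating therapists rate the ADIS-IV-C and CGI. The article does not support that. Outcome measures gives the timing of the ADIS-IV-C but not the interviewer, and the CGI description refers only to the clinician. That these ratings are unmasked is a reasonable inference from the open-label statement, but no sentence says so of the raters.

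A reader might also infer that present staff could provide masked rating at no cost. No staff numbers are given. The eligibility interview takes about 90 minutes with parent and child together, and repeating it twice across two universities for up to about 165 families raises travel or remote-interview questions. Masking would also be fragile: one program uses a website and many online parent sessions, the other two individual parent sessions, and parents take part in the interview.

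The direction of bias is also open. The Objectives expect the new program to be as effective as Coping Cat, which could draw the arms together. The Discussion expects better adherence, less dropout and better transfer, which could favour one arm. If families in both arms over-report improvement equally, that alone leaves the between-arm difference unchanged.

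None of this defends having therapists collect and enter the outcomes when research assistants are named for the same work.

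**Conclusion.** The point holds for the self-report questionnaires. Therapists are expressly among those who administer and enter the primary RCADS and CALIS, they have access to the database, and the trial is open label. This is a stated choice, not a detail left out, and it can be changed cheaply.

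Its size is not known. The rise in false equivalence from 5% to between 14.5% and 32% assumes a shrinkage of 20% to 40% and a true difference exactly at the margin. The fall in power from about 80% to 54% assumes a differential bias of 0.2 SD with equal arms. A reader might take these as errors that the change would prevent. They are not, because children and parents report their own symptoms knowing their treatment, whoever hands over the form. Separating the roles removes therapist influence on answers and entry, and leaves that reporting bias in place. The case for the change does not depend on which way the bias runs.

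For the ADIS-IV-C and CGI, the conclusion is limited to a clarification: the post-allocation rater should be named.

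**What to change.** In Data management, state that the mid-treatment, posttreatment and follow-up questionnaires are administered and entered by research assistants who did not lead or observe that child's group. Observers need to be mentioned because Treatment fidelity places one in each session. Remove therapists' access to outcome data while the trial runs. Forms that only a therapist can complete, such as the adherence checklist and the involvement-in-therapy ratings, are unaffected.

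In Outcome measures, name who conducts the ADIS-IV-C and rates the CGI after allocation. Where current staffing allows, this should be a team psychologist who did not treat the child. Masked rating, or rating by the other university's team, is desirable, but the article does not show that it is feasible, so it should be adopted only if capacity is confirmed.

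The cost of the questionnaire change is some scheduling effort. The sample size, the interventions and the analysis stay as they are.

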### Statistical methods

#### Efficacy evaluation

The efficacy of the Emotion Detectives In–Out in comparison with the Coping Cat will be assessed by analyzing the changes in the primary and secondary outcomes. As an equivalence clinical trial, the aim is to test whether the Emotion Detectives In–Out (experimental condition) is as effective as the Coping Cat (control group). The planned analysis for each outcome is a repeated-measures linear mixed model adjusted for covariates. The primary equivalence testing will be the between-group difference TOST at postintervention and at 3 months using the Welch correction for heterogeneous variance if needed. We will also investigate the linear and nonlinear (quadratic) effects for time and condition and simple effects for parameter estimates within each condition. For categorical variables (e.g., treatment response as assessed by CGI-I), treatment conditions will be compared using Pearson’s chi-square test.

To examine for heterogeneous intervention response, we will calculate Reliable Change Indices (RCI) for all participants at postintervention and at the 3-month follow-up. The RCI will be calculated for all outcomes and correlated with demographics to examine for subgroup efficacy predictors. The cutoff for clinically significant change is generally accepted as ± 1.96 [81]. Likewise, we aim to test the longitudinal trajectory of anxious symptoms over time using Growth Mixture Modeling (GMM). Furthermore, assuming that heterogeneous trajectories of anxious symptoms are observed, we aim to test the suitability of the collected demographic variables as predictors of group membership.

For the primary equivalence, efficacy, RCI, and chi-square analyses, we will use Jamovi software and the GAMLj and TOSTER packages as needed [82]. For GMM analyses, we will use R software with the package *lccm* [83] to perform growth mixture modeling, and evaluate various model specifications of *k* classes two through six, and using both fixed and random effects. We will select the optimal number of clusters was based on four criteria: parsimony, entropy approaching 1, lowest BIC/SABIC, and minimum class size > 10% of the sample [84, 85].

Following Kennedy, Bilek [19], the attainment of diagnostic remission for both the principal diagnosis and all emotional disorder diagnoses at posttreatment and follow-up will be defined as the absence of the principal diagnosis and the absence of all emotional disorder diagnoses, respectively (i.e., ADIS-IV CSR < 4). A CGI-I score of 1 (*very much improved*) or 2 (*much improved*) at posttreatment or follow-up will be considered an indication of a meaningful reduction in the severity of emotional disorders and will be deemed indicative of a positive treatment response, consistent with the findings from other studies [19, 86].

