#### Randomization

##### Sequence generation

After the children and parents fill out the baseline (T0) assessment measures, they will be randomly assigned at each recruitment location by a researcher not collaborating in the study and through an automated, web-based randomization program to one of two conditions: the experimental condition (Emotion Detectives In–Out) and the active control condition (Coping Cat). A permuted block randomization procedure will be employed in each location to obtain groups with an equivalent number of participants. The block size will depend on the number of eligible children in each location, but it is expected to be between 10 and 12 so that 5 to 6 participants can be assigned to each condition.

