#### Planned and post hoc examination of potential confounds and moderator effects

##### Covariates

Variables that are expected to correlate with but not predict outcomes differentially will be included in the baseline model to account for their effect. The targeted covariates include sociodemographic and clinical variables, such as the children’s age and sex, number of comorbid disorders, use of psychopharmacological medication, and previous psychological treatment.

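### The primary equivalence test is not tied to the planned adjusted mixed model, and neither the baseline score nor the randomisation location is named as an adjuster, so precision is probably lost and two verdicts are possible

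*Protocol article*

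**What the plan says.** All references are to the protocol article.

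- **Statistical methods, Efficacy evaluation** opens by saying that efficacy "will be assessed by analyzing the changes in the primary and secondary outcomes". It then states: "The planned analysis for each outcome is a repeated-measures linear mixed model adjusted for covariates". The next sentence gives the equivalence decision to a test: "The primary equivalence testing will be the between-group difference TOST at postintervention and at 3 months using the Welch correction". The correction is conditional: "using the Welch correction for heterogeneous variance if needed". On software: "we will use Jamovi software and the GAMLj and TOSTER packages as needed".
- **Covariates** names the child's age and sex, the number of comorbid disorders, "use of psychopharmacological medication, and previous psychological treatment". The list is introduced as examples, and the covariates are assigned to a baseline model. Neither the T0 score of the outcome nor recruitment location is on it.
- **Randomization, Sequence generation**: T0 measures are completed before assignment, and "A permuted block randomization procedure will be employed in each location".
- **Sample size**: 138 children (69 per group), from a TOST with d = 0.50, alpha 0.05, 80% power, equal allocation and four measurements.

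**The concern.** Two analyses are named and the text does not say how they relate. A Welch correction belongs to a two-sample comparison of means, not to a contrast from a mixed model. The wording therefore suggests that the decision rests on a comparison without covariates, while the adjusted model runs alongside.

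Two things follow. First, a T0 score measured before randomisation is the natural covariate for an anxiety score after treatment. Leaving it out makes the confidence interval wider than it need be, and in an equivalence trial the width of that interval decides the result. Second, the two analyses will give different intervals. Near the margin one could show equivalence and the other not, and the text does not say outright which governs.

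**Working it through.** **Inputs.** Margin 0.50 SD, alpha 0.05 for each one-sided test, 80% power and 69 per arm come from Sample size. Three inputs are assumptions: a true difference of 0, the baseline-to-post correlation r, and the share L of outcome variance explained by location. The documents give neither r nor L, so ranges are used. All power figures are for one measure at one time point.

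**Step 1: reproduce the plan's figure.** Unadjusted two-sample TOST, normal approximation:

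n per arm = 2 × ((z₀.₉₅ + z₀.₉₀) / d)² = 2 × ((1.645 + 1.282) / 0.5)² = 68.5, rounded up to 69.

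This matches, with no term for baseline, location or repeated measures. Other simple formulas do not match: a single one-sided test gives 50, a two-sided superiority test 63, and a TOST at alpha 0.025 gives 85. Power at 69 per arm is 80.4% (normal) or 79.9% (t-based).

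**Step 2: adjust for baseline.** Adjustment multiplies the variance by (1 − r²), so SE = √(2(1 − r²)/69) in SD units. Normal-approximation power is 2Φ(0.50/SE − 1.645) − 1. The last column shows a TOST on change scores, with variance factor 2(1 − r).

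| r | SE | 90% CI half-width | Power, normal | Power, t-based | Change-score power, normal |
|---|---|---|---|---|---|
| 0 | 0.170 | 0.280 | 80.4% | 79.9% | 33.4% |
| 0.3 | 0.162 | 0.267 | 84.8% | 84.4% | 59.8% |
| 0.5 | 0.147 | 0.243 | 91.9% | 91.6% | 80.4% |
| 0.6 | 0.136 | 0.224 | 95.7% | 95.5% | 89.9% |

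At r = 0.5 the gain equals that of 69 / (1 − 0.25) = 92 children per arm in an unadjusted analysis. Change scores are less precise than baseline adjustment at every r below 1, because 1 − r² = (1 − r)(1 + r) is then smaller than 2(1 − r).

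**Step 3: add location.** With variance factor 1 − L and no baseline term, normal-approximation power is 81.4% (L = 0.02), 82.9% (L = 0.05) or 85.3% (L = 0.10). That is a gain of about 1 to 5 points. With r = 0.5 and L = 0.05 it is 93.8%.

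**Step 4: check the margin's scale.** The gains need a margin fixed in total-SD units. If d = 0.50 were standardised by the residual SD of the adjusted model, the margin at r = 0.5 would be 0.50 × √0.75 = 0.433 total SD. Then 0.433/0.147 is the same ratio as 0.50/0.170, about 2.94, and the gain disappears.

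Which SD is used also matters. Suppose the margin is 0.50 baseline SD and the post SD is 1.2 times the baseline SD (an illustration). The adjusted SE at r = 0.5 is 1.2 × 0.147 = 0.177 and power is about 76%. The unadjusted SE is 1.2 × 0.170 = 0.204 and power is about 58% (0.50/0.204 − 1.645 ≈ 0.80; 2 × 0.789 − 1 ≈ 0.58). Adjustment still helps at a given margin, but 92% is not guaranteed.

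**The case against.** A reader might infer that the plan fixes a Welch test on raw post-treatment scores and excludes the baseline. The text does not go that far. The Welch correction is conditional. Post scores are never specified, and the section's opening speaks of changes; a change-score TOST would use T0. The covariate list is open, and T0 is presumably one of the measurements in the repeated-measures model. The mixed model and the TOST sit side by side, and the software sentence lists GAMLj with TOSTER, so a TOST on the model's contrast is not ruled out. The match at 69 per arm shows that the sizing credits no gain from adjustment; it does not prove how the data will be analysed. A change-score TOST at r = 0.5 gives 69 as well.

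A reader might also infer that omitting location makes the test invalid, or that the trial is too small. Neither is supported. The unadjusted comparison is unbiased, and its interval already allows for chance imbalance. Leaving out a stratification factor tends to make the SE too large, which is conservative for equivalence. On its own assumptions the trial has about 80% power.

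Finally, covariate lists and contrast specifications are commonly left to the analysis plan. That is fair for the detail. It does not dispose of the point, because the article itself names the primary test and sets it apart from the adjusted model. What stands is an unclear link between the two analyses, with a natural reading that gives up precision.

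**Conclusion.** The point holds as one of lost efficiency and an ambiguous decision statistic, not of invalidity. The natural reading is an unadjusted primary TOST, with the T0 score and location not named as adjusters anywhere.

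Using t-based figures, with 69 per arm and a fixed margin of 0.50 SD, baseline adjustment would take power from about 80% to about 84%, 92% or 96% for r = 0.3, 0.5 or 0.6. These figures assume a true difference of zero and equal SDs at baseline and afterwards, and they precede any loss from treating children in groups. Nearly all the gain comes from the baseline score. If the TOST is meant for change scores, baseline adjustment is still the more precise choice. The change is worth making because the unadjusted design has no power to spare.

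**What to change.** State in Efficacy evaluation that equivalence at postintervention and at 3 months is judged by the 90% CI of the adjusted between-group difference at that time point, taken from the mixed model already planned. Include the T0 score of the same measure and recruitment location together with the listed covariates. Convert the d = 0.50 margin to scale points in advance using a stated total SD, not the model's residual SD, so that the margin does not shrink as adjustment improves. Keep the two-sample TOST as a sensitivity analysis and say which scores it uses.

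The cost is a few sentences, plus choosing and justifying the SD for the conversion. No new data or recruitment is needed, because T0 and location are already recorded. The TOST is computed from the model's estimate and SE instead of from a two-sample routine.

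### Categorical outcomes such as CGI-I response are given only a Pearson chi-square test, which has no margin and so cannot support this trial's equivalence aim on those endpoints

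*Protocol article*

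**What the plan says.** All references are to the protocol article.

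- **Aim.** Statistical methods, Efficacy evaluation, says that efficacy "will be assessed by analyzing the changes in the primary and secondary outcomes", and states the purpose: "As an equivalence clinical trial, the aim is to test whether the Emotion Detectives In–Out (experimental condition) is as effective as the Coping Cat".
- **Equivalence test.** The same paragraph says: "The primary equivalence testing will be the between-group difference TOST at postintervention and at 3 months".
- **Categorical outcomes.** The same paragraph gives one method: "For categorical variables (e.g., treatment response as assessed by CGI-I), treatment conditions will be compared using Pearson’s chi-square test". No margin or confidence-interval rule for a proportion is attached to it.
- **Binary definitions.** Later in the same subsection, a CGI-I score of 1 or 2 "will be deemed indicative of a positive treatment response". Remission of the principal diagnosis and of all emotional disorders "will be defined as the absence of the principal diagnosis and the absence of all emotional disorder diagnoses, respectively (i.e., ADIS-IV CSR < 4").
- **Status of the instruments.** Both instruments are listed under Primary outcome measures. Under Anxiety symptoms: "Changes in anxiety will be assessed through the ADIS-IV-C". The two CGI scales follow under Symptom severity and improvement.
- **Margin.** Trial design describes the margin as the smallest clinically relevant difference. Sample size gives its only value, d = 0.50, which is a standardized mean difference.

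**The concern.** The named test does not answer the question the trial asks. A chi-square test starts from equal proportions and looks for evidence against that. Equivalence starts from a difference at least as large as the margin and looks for evidence against that. The two nulls are opposed, so no chi-square result, significant or not, shows that response rates lie within a margin.

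The affected endpoints matter to readers. They are the clinician-rated response and, by its definition, diagnostic remission, and both derive from instruments listed as primary. A difference test also rewards imprecision: the smaller or noisier the trial, the more often it finds no difference. For the continuous scores the protocol avoids this by using TOST. For the categorical outcomes it states no counterpart.

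This is more than detail left to an analysis plan, because the protocol names a specific test and that test does not fit the stated aim.

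**Working it through.** **1. The plan's own sample size.** Inputs from Sample size: margin d = 0.50, alpha 0.05 for each one-sided test, power 80%, 1:1 allocation. For TOST with a true difference of zero,

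n per arm = 2 × (z₀.₉₅ + z₀.₉₀)² / d² = 2 × (1.645 + 1.282)² / 0.25 = 68.5, so 69 per arm and 138 in total.

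This reproduces the stated figure. It is a calculation for a standardized mean difference and gives no assurance about proportions. About 165 are to be recruited, or about 82 per arm (165 / 2 = 82.5). The Attrition, nonadherence and missing data section plans intention-to-treat with multiple imputation, so both 69 and 82 per arm are shown.

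**2. Translating the margin to a proportion.** The protocol gives no response or remission rates, so control rates of 50–80% are assumed. If response reflects a latent normal score (also an assumption), a deficit of d = 0.50 moves a control rate p to Φ(Φ⁻¹(p) − 0.50).

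**3. Chi-square at that deficit.** The table gives the probability that the uncorrected Pearson chi-square is non-significant at 0.05, by exact enumeration of two independent binomials. Clustering by therapy group is ignored.

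| Control rate | Rate at d = 0.50 worse | Gap (points) | Non-significant, 69 per arm | Non-significant, 82 per arm |
|---|---|---|---|---|
| 50% | 30.9% | 19.1 | 37% | 30% |
| 60% | 40.3% | 19.7 | 35% | 28% |
| 70% | 51.0% | 19.0 | 38% | 30% |
| 80% | 63.4% | 16.6 | 41% | 34% |

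If equivalence were instead declared only when the 90% Wald interval for the risk difference lies inside a margin equal to that gap, the same enumeration gives a false declaration in about 5% of trials, as TOST is designed to do.

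**4. One illustrative result.** With 48/69 (69.6%) against 38/69 (55.1%), chi-square gives p = 0.079. The 90% interval for the difference runs from 1.1 to 27.9 points. The test is non-significant, yet the data are compatible with a deficit well beyond 20 points.

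**5. What an equivalence test could deliver.** Take 60% response in both arms and 69 per arm:

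- SE = √(2 × 0.6 × 0.4 / 69) = 0.0834.
- 90% interval half-width = 1.645 × 0.0834 = 0.137, about 14 points.
- Power = 2Φ(margin/SE − 1.645) − 1, which is about 12% at ±15 points and 55% at ±20 points.

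Exact enumeration gives 11% and 57%, in close agreement.

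**The case against.** The strongest reply is that the protocol keeps the chi-square apart from its equivalence inference. TOST is named as the primary equivalence test, the sample size rests on it, and the software paragraph lists equivalence and chi-square analyses as separate items. A difference test on response rates beside a TOST is a legitimate supplementary analysis if nobody misreads it. This stands, and it confines the point to the categorical endpoints.

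A reader might infer that the authors intend to read a non-significant chi-square as equivalence. The document does not say so. It says only that the conditions will be compared, and it neither adopts nor rules out that reading.

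A reader might also infer that response and remission are primary equivalence endpoints tested wrongly. The instruments are listed as primary, but neither dichotomy is called a primary equivalence endpoint. Remission is not named in the chi-square sentence; it comes in as a categorical variable through its definition.

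Larger miss rates are tempting. At 69 per arm, chi-square is non-significant in 56% of trials at 70% against 55%, and in 77% at 70% against 60%. But gaps of 10 and 15 points lie inside a 20-point margin, so these figures partly count programs that an equivalence test at that margin would treat as equivalent. The fair comparison is at a gap matching the trial's own margin.

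Finally, a proportion margin could be set in an analysis plan not shown here. That is true of the margin's value, but it does not remove the mismatch between the test the protocol names and the aim it states.

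**Conclusion.** The point holds as a moderate one. For categorical outcomes the protocol names a test that cannot support its stated equivalence aim. The TOST comparison of continuous scores, and the sample size built on it, are not affected.

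If a non-significant chi-square were taken to mean equal efficacy, a deficit equal to the d = 0.50 margin (about 17–20 points) would pass in about 35–41% of trials at 69 per arm and 28–34% at 82 per arm, instead of about 5%. This rests on assumed control rates of 50–80%, the probit conversion of d, and independent observations. It also depends on a reading of the test that the protocol leaves open but does not state. For that reason, and because the main equivalence conclusion does not depend on chi-square, the point is not a must-fix.

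**What to change.** - For CGI-I response and ADIS remission, replace or accompany chi-square with the risk difference and its 90% confidence interval. Judge it against a percentage-point margin that is justified and fixed before data lock.
- Label these endpoints supportive of the TOST on continuous scores.
- State that a non-significant difference will not be described as equivalence.

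The cost is analysis wording only, with no added data collection and no change to the sample size. The drawback is limited power: at the 12% and 55% shown for margins of ±15 and ±20 points, these results will often be inconclusive and should be reported as such.
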